### Study design

2.5

Eligible participants were randomly assigned to the treatment group or control group at a ratio of 1:1 using a random tool based on the central network. Randomization was performed without any stratification using SAS 9.3 software (SAS Institute, Cary, NC, USA) by independent statisticians who were not involved in the implementation of the experiment or statistical analysis. Randomization was performed without any stratification. The clinical research coordinator enters participant information on the tablet and is given a random number. The research assistant gets the participant's assignment from the computer. Throughout the research process, the research assistant is responsible for screening, recruiting participants, and assigning random numbers to the included participants. The result assessor is responsible for the assessment of the scale. All bed doctors, researchers, research assistants, participants, intervention supervisors, and statisticians who perform statistical analysis are unknowable in the grouping of personnel.

The dispensation of medicines will be assigned to patients with corresponding numbers by unknowing nurses according to the medicine numbers.

### Intervention

2.6

Control group: Oral vardenafil hydrochloride tablets, 20 mg/time, 1 time/d;

Treatment group: Oral bosentan tablets on the basis of the control group, according to the weight of the patient, weight <10 kg: 15.625 mg/time; weight: 10 to 20 kg: 31.25 mg/time; weight: 21 to 40 kg: 62.5 mg/time, 1 time/d.

The treatment lasts for 6 months. During the treatment period, the patients will be followed up by outpatient or telephone in the first and third months of treatment to understand the symptoms and adverse reactions of the patients, and review the observation indicators at the sixth month.

### Observation index

2.7

1.Oxyhemoglobin saturation SpO2, using GEM3000 blood gas analyzer to measure SpO2 before and after treatment in the 2 groups;2.(2) 6-min walking test distance (6 MWTD): For children who can cooperate with walking to walk back and forth in a quiet and airy 30-m corridor, measure the 6-min walking distance;3.The patient uses a SwanGanz floating catheter for right heart catheterization in a resting state to determine systolic pulmonary artery pressure, pulmonary artery pressure, and aortic pressure. Fick method is used to calculate mean pulmonary artery pressure, pulmonary circulation blood flow quantity/systemic circulation Blood flow quantity, pulmonary artery systolic pressure/systemic artery systolic pressure;4.The patient got 5 ml of fasting venous blood in the morning before and after treatment, and the brain natriuretic peptide was measured by enzyme-linked immunosorbent assay;5.Borg score^[9]^ (divided into 0–10 grades, 10 is the most serious, consciously exhausted), cardiac function classification (NYHAFC);^[10]^6.Adverse reactions: including dizziness, headache, facial flushing, abnormal liver, and kidney function, etc.

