### Sample size

2.3

The calculation of the sample size is based on the results of the 6 MWTD. According to the results of the pre-test, the average score of the experimental group is estimated to be 495.47 and the standard deviation is 54.72. The control group averaged 456.33 and the standard deviation was 54.68. The sample size calculation formula is as follows$$n=n1=n2=\frac{{\left(u_{\alpha }+u_{\beta }\right)}^{2}\times \sigma^{2}}{\delta^{2}}\times 2$$

At the 5% significance level, a total of 34 patients are required for each group to achieve 90% power. The estimated withdrawal rate is 20%, and 42 patients will be included in each group.

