### Patients

2.4

Inclusion criteria:

1.All patients meet the diagnostic criteria of congenital heart disease-pulmonary hypertension (CHD-PAH),^[8]^ aged> 6 months and <16 years old;2.There is a risk of reactive pulmonary hypertension or pulmonary hypertension at the end of the operation Phenomenon;3.postoperative pulmonary artery systolic pressure/systemic arterial systolic pressure (Pp/Ps) ≥0.3, no decrease within 1 week;4.patients with moderate or higher pulmonary hypertension found in postoperative follow-up;5.preoperative pulmonary vascular resistance index (PVRI) ≥4 persons.

Exclusion criteria:

1.Children with other types of pulmonary hypertension related to non-congenital heart disease;2.Patients with liver and kidney dysfunction;3.Patients with prolonged QT syndrome;4.Patients concurrently using antiarrhythmic drugs;5.Allergic to test drugs;6.Severe digestive system or blood system abnormalities;7.Unable to understand after explanation.

The research protocol may be unwilling to participate.

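### The 42 per group allow for 20% withdrawal only, so any share of children who cannot do the six-minute walk takes the trial below its stated 34 evaluable per group and 90% power

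*Protocol article*

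**What the plan says.** Section 2.3 (Sample size) names one measure as the basis for the trial's size: "The calculation of the sample size is based on the results of the 6 MWTD". The planning values come from a pre-test: "the average score of the experimental group is estimated to be 495.47 and the standard deviation is 54.72", and "The control group averaged 456.33 and the standard deviation was 54.68". The result is "At the 5% significance level, a total of 34 patients are required for each group to achieve 90% power", followed by "The estimated withdrawal rate is 20%, and 42 patients will be included in each group". Withdrawal is the only allowance made.

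Section 2.4 (Patients) sets the age range as "aged> 6 months and <16 years old". No criterion there concerns walking ability or a minimum age for the test. Section 2.6 (Intervention) has a separate weight band below 10 kg, so very small children are expected. It also ends treatment, and schedules the final review of the indicators, at six months.

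Section 2.7 (Observation index) then limits who does the walk: "For children who can cooperate with walking to walk back and forth in a quiet and airy 30-m corridor". It does not say when that ability is judged.

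**The concern.** Read together, these sections do not fit. The sample size treats every child who does not withdraw as supplying a walk distance, yet the protocol itself foresees children who will not do the test. The youngest do not grow into it during the trial: a child of 7 months at entry is 7 + 6 = 13 months old at the final review.

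Two things are at stake. First, the only stated justification for the trial's size describes more evaluable children than the design can be expected to deliver. Second, ability to cooperate is not tied to a time before randomisation. If it were judged at month 6, a child whose condition changed during treatment could enter or leave the analysed set because of that change, and the set would no longer be fixed by randomisation.

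**Working it through.** **Inputs.** From section 2.3: means 495.47 and 456.33, SDs 54.72 and 54.68 (54.70 used), 5% significance level, 90% power, 20% withdrawal, 42 enrolled per group. From section 2.5 (Study design): "randomly assigned to the treatment group or control group at a ratio of 1:1". The share f of children unable to do the walk is not in the document. It is assumed here, over 0 to 50%, and taken to be equal in both groups and unrelated to withdrawal.

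**Step 1: reproduce the stated 34.** The difference is 495.47 − 456.33 = 39.14, or 39.14/54.70 = 0.716 SD. The article's formula is n = 2(u_α + u_β)²σ²/δ².

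- One-sided 5%: 2 × (1.645 + 1.282)² × 54.70²/39.14² = 33.45, rounded up to 34. This matches.
- Two-sided 5%: 2 × (1.960 + 1.282)² × 54.70²/39.14² = 41.04, rounded up to 42. This does not match the 34.

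The article does not state sidedness. The one-sided footing is used as the main one below because it is the one that gives the stated figure.

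**Step 2: look for slack in the 42.** 42 × (1 − 0.20) = 33.6, against 34 needed. Withdrawal uses the whole inflation.

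**Step 3: add children who cannot do the walk.** Evaluable per group = 42 × 0.8 × (1 − f), rounded down. Power is from the noncentral t distribution with standardised difference 0.716. The last column is 34/[0.8 × (1 − f)], rounded up.

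| Assumed f | 42 × 0.8 × (1 − f) | n used | Power, one-sided 5% | Power, two-sided 5% | Enrolment per group that keeps 34 evaluable |
|---|---|---|---|---|---|
| 0% | 33.6 | 33 | 89% | 82% | 43 |
| 10% | 30.2 | 30 | 86% | 78% | 48 |
| 20% | 26.9 | 26 | 82% | 72% | 54 |
| 30% | 23.5 | 23 | 77% | 66% | 61 |
| 40% | 20.2 | 20 | 72% | 60% | 71 |
| 50% | 16.8 | 16 | 63% | 50% | 85 |

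**Step 4: separate the two causes.** At f = 0 the one-sided figure is 89%, so rounding 33.6 down costs about one point. The two-sided figure at f = 0 is 82%; almost all of that drop from 90% comes from sidedness, not from non-walkers. The loss that belongs to this point is the fall down each column. One-sided, that is about 3 points at f = 10%, 7 at 20%, 12 at 30%, 17 at 40% and 26 at 50%.

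**Step 5: check sensitivity to method.** With the normal approximation and no rounding, the one-sided figures are 90%, 87%, 84%, 79%, 74% and 67%. The pattern is the same, and the decline is slightly shallower.

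**The case against.** The strongest reply is that the size of the loss is unknown. The article gives no share of non-walkers, and if few infants are enrolled the loss is a few points. That stands, and it is why the figures are a range. It does not remove the inconsistency, because 33.6 is already under 34 and there is nothing to absorb even a small share.

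A second reply is that the last exclusion criterion in section 2.4, on inability to understand after explanation, removes these children. It mentions neither age nor walking. Read as a filter on the child, it would conflict with the lower age limit and with the weight band below 10 kg.

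A third is that failing to walk because of infancy is an age trait, present before randomisation and independent of group, so comparing walkers is largely still a randomised subgroup comparison. Section 2.9 also plans an analysis over time, which suggests a baseline measurement. This is fair. A reader might infer that the walk comparison is necessarily made in a post-randomisation subset. The document does not say that; it leaves the time point open, and only children who gain or lose the ability during treatment would cause the problem.

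The limitations in section 3 concede that age may affect the results. That does not repair the sample size.

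**Conclusion.** The point holds as an inconsistency between sections 2.3, 2.4 and 2.7. The stated 34 evaluable per group and 90% power require that essentially every child who does not withdraw can do the walk, and the protocol does not expect that. On the one-sided footing, power is about 86% at an assumed 10% of non-walkers, 82% at 20% and 63% at 50%. These figures rest on the assumed share, on the article's own planning values and on equal shares in the two groups. Possible dependence of the analysed set on post-randomisation status is a risk left open, not an established bias.

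Some stronger readings are not supported:

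- **Power of 82% blamed on non-walkers.** That figure applies with no non-walkers at all and reflects a two-sided test. Sidedness is a separate matter.
- **A planning SD too small for the age range.** Only children who can walk supply a distance, so an SD from walkers is the right kind of input. The ages in the pre-test are not given, and the document offers no larger value.
- **The same defect in the Borg score.** The article does not say that every child rates it unaided, section 2.5 assigns scale assessment to an assessor, and no sample size rests on it.
- **Catheter pressure as a ready substitute.** Section 2.7 does not show that it is measured in every child at month 6.

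**What to change.** Record before randomisation whether each child completes a baseline six-minute walk. Define the walk-distance analysis set as all randomised children able at baseline, whatever their status at month 6. In section 2.3, state the expected share of such children and restate the evaluable number and power for that set. Limit the walk-distance conclusion to children able to walk the test. Stratifying randomisation on this yes/no item is optional.

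The cost is some protocol wording, one item recorded at baseline, a lower stated power, and a walk-distance conclusion that does not extend to the youngest eligible children. If the sponsor prefers to keep 34 evaluable per group, the price is the larger enrolment in the last column of the table: for example, 54 per group at an assumed 20% of non-walkers, on the one-sided footing.

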### Data collection and management

2.8

One or 2 assistants will collect and record the entire data. Personal information about potential participants and registered participants will be collected, shared and stored in an independent storage room to protect confidentiality before, during and after the test. The access to the database will be restricted to the researchers in this study team.

### Statistical analysis

2.9

Data were analyzed using the statistical software package SPSS version 25.0 (Chicago, IL). Continuous variables were described as the mean ± standard deviation, and differences between groups were analyzed using a series of one-way analysis of variance (ANOVA) with Bonferroni posthoc test, while differences between groups over time were analyzed using multiway ANOVA with Bonferroni posthoc test. Categorical variables were described as the number (%), and were analyzed by Fisher exact test. A *P* value of <.05 was considered statistically significant.

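### Section 2.9 analyses BNP by ANOVA with no transformation and no baseline covariate, which can cost power for this secondary index but does not inflate type I error

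*Protocol article*

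**What the plan says.** Observation index (2.7) lists BNP among the outcomes, from fasting blood drawn before and after treatment: "the brain natriuretic peptide was measured by enzyme-linked immunosorbent assay". The protocol gives no BNP mean, SD or range.

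Statistical analysis (2.9) then sets a single rule for continuous data. The summary is "Continuous variables were described as the mean ± standard deviation". For the comparison of arms, "differences between groups were analyzed using a series of one-way analysis of variance (ANOVA) with Bonferroni posthoc test". For change over time, "differences between groups over time were analyzed using multiway ANOVA with Bonferroni posthoc test". The threshold is a P "value of <.05 was considered statistically significant". The section mentions no transformation, median, rank test or covariate, and exempts no variable.

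BNP is not the outcome that sizes the trial: "The calculation of the sample size is based on the results of the 6 MWTD".

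**The concern.** BNP is a concentration and cannot fall below zero. The trial admits children from 6 months to under 16 years who qualify by several indicators of severity, so a long upper tail is plausible. If there is one, a few high values inflate the SD. The mean and SD then describe the group poorly, and a real proportional reduction is harder to detect.

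Separately, the plan collects BNP before treatment but does not use it as a covariate. With two arms, the one-way ANOVA is the two-sample t test on the values after treatment. It ignores what each child's baseline predicts about the later value.

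What is at stake is the chance of detecting a true BNP effect and the clarity of its description. The main comparison and the size of the trial are not affected.

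**Working it through.** **The plan's own figure.** There is none for BNP, so the per-group number is borrowed from the 6-minute walk calculation in section 2.3. The inputs there are "the average score of the experimental group is estimated to be 495.47 and the standard deviation is 54.72" and "The control group averaged 456.33 and the standard deviation was 54.68". The difference is 495.47 − 456.33 = 39.14 and the pooled SD is 54.70. At one-sided 5% and 90% power, n = 2 × (1.645 + 1.282)² × 54.70² / 39.14² ≈ 33.45, so 34 per group, as stated. (Two-sided 5% gives 41.04, so 42. The protocol does not state sidedness; that is a separate matter.) I use 34 per group below, with two-sided 5% tests.

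**Assumed inputs, not in the protocol.** BNP is log-normal with the same log-scale SD, *s*, in both arms. The geometric mean is 40% lower with the combination. The correlation between log baseline and log month-6 BNP is 0.6. *s* is varied.

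**Closed-form approximation for the two log-scale analyses.**
- Effect: |ln 0.6| = 0.511. Standard error: *s* × √(2/34) = 0.2425*s*.
- Log ANOVA: power ≈ Φ(0.511 / 0.2425*s* − 1.96) = Φ(2.106/*s* − 1.96).
- Log ANCOVA: the residual SD is *s* × √(1 − 0.6²) = 0.8*s*, so power ≈ Φ(2.633/*s* − 1.96).
- At *s* = 0.6: Φ(1.55) = 94% and Φ(2.43) = 99%. At 0.8: Φ(0.67) = 75% and Φ(1.33) = 91%. At 1.0: Φ(0.15) = 56% and Φ(0.67) = 75%.

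The untransformed test has no such simple form and was simulated together with the other two. The simulated log-scale powers are slightly below the approximation because they use the t distribution.

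| log-SD | ANOVA, untransformed | ANOVA, log | ANCOVA, log | gain from log step | further gain from baseline |
|---|---|---|---|---|---|
| 0.45 | 99% | about 100% | about 100% | about 1 | about 0 |
| 0.6 | 89% | 93% | 99% | 4 | 6 |
| 0.8 | 62% | 74% | 90% | 12 | 16 |
| 1.0 | 38% | 53% | 72% | 15 | 19 |

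**Share of the gain due to baseline adjustment,** with the log step taken first: 6/10 = 60%, 16/28 = 57% and 19/34 = 56% at log-SD 0.6, 0.8 and 1.0. The split would differ if the steps were taken in the other order.

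**Check without a ceiling near 100%.** A second simulation reset the effect at each log-SD so that the log-scale test had nominal 80% power. Log against untransformed power was 79% vs 77% at log-SD 0.3, 79% vs 74% at 0.5, 78% vs 68% at 0.75 and 79% vs 60% at 1.0. The loss is trivial under mild skew and grows with it.

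**Type I error.** With no true effect, the untransformed test rejected in 3.1% to 5.2% of trials over log-SD 0.3 to 1.5. The log-scale analyses rejected in about 4% to 5.5%.

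**Does the planned over-time ANOVA make up for this?** Read as a repeated-measures group-by-time model with two BNP measurements, its interaction is a t test on untransformed change. Its simulated power was 82%, 51% and 30% at log-SD 0.6, 0.8 and 1.0, below even the one-way ANOVA.

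**The case against.** The strongest objection is that the protocol contains no BNP data. Skew is an inference from the kind of measurement and the mixed population. With mild skew the log step gains almost nothing. This stands, and it is why the power loss from scale is stated only as conditional.

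Second, this is a condensed article, and transformation of one biomarker is a detail that an analysis plan might settle. ANOVA on log values is still ANOVA, and section 2.9 never uses the word untransformed. This stands in part: the scale of the test is inferred from silence. But the section does state a rule for every continuous variable, and a mean and SD for BNP is what that rule prescribes. The point criticises a choice that was made.

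Third, a good part of the improvement has nothing to do with skew. It comes from the baseline covariate, which would help other outcomes too. This also stands, so the two sources of gain are shown separately above.

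A reader might infer that the BNP test is invalid, or that a few extreme children could produce a false positive. The type I error figures do not support that; the cost is power. A reader might also infer that the trial is too small because of BNP. Section 2.3 sizes it on walking distance, so the 34 and 42 per group do not depend on BNP.

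**Conclusion.** The point holds as a minor improvement to the analysis of a secondary index. As written, section 2.9 analyses BNP without transformation and without its measured baseline as covariate. This can lower power but does not raise the false-positive rate.

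Moving to log ANCOVA adds about 1 point of power at log-SD 0.45, 10 at 0.6, 28 at 0.8 and 34 at 1.0. From 0.6 upwards, rather more than half of that is baseline adjustment. These sizes rest on four assumptions that the protocol neither gives nor contradicts: log-normal BNP, the log-SD, a 40% lower geometric mean and a baseline correlation of 0.6.

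That BNP is in fact strongly skewed, or that the choice of scale alone explains the lost power, goes further than the document allows.

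**What to change.** Add to section 2.9 that BNP at month 6 is log-transformed and compared between arms by ANCOVA with log baseline BNP as covariate. The result is reported as the ratio of geometric means with its 95% confidence interval, and BNP is described by median and quartiles in each arm. Writing this down before the data are seen also removes a later, data-driven choice of scale.

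The cost is analysis wording only. Baseline BNP is already collected, so no patients, visits or samples are added. The small downside is that the effect is a ratio rather than a difference in concentration.

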Some studies have pointed out that bosentan combined with vardenafil or sildenafil is better than monotherapy in the treatment of pulmonary hypertension after congenital heart disease in children,^[7,19]^ in 2015 the European Society of Cardiology (ESC) pulmonary artery. The guidelines for the diagnosis and treatment of hypertension recommend starting oral drug combination therapy for patients with cardiac function class II to III.^[20]^ The combination therapy is becoming more and more important for the treatment of pulmonary hypertension after children with congenital heart disease. This study will be evaluated the effect of bosentan combined with vardena on the treatment of pulmonary hypertension after nonchildren's congenital heart disease.

This study also has the following limitations: Since this is a singlecenter randomized controlled study, the included population may be regionalized, and the results may be biased; factors such as the age of the patients included in the study may have an impact on the results.

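### The stated between-group test uses no covariate after unstratified randomisation over a very wide age range; it is valid, but an ANCOVA on baseline value and age would probably be more precise at little cost

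*Protocol article*

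**What the plan says.** Section 2.9 of the protocol article names two analyses for continuous variables. First, "differences between groups were analyzed using a series of one-way analysis of variance (ANOVA) with Bonferroni posthoc test". Second, "differences between groups over time were analyzed using multiway ANOVA with Bonferroni posthoc test". The factors of the second are not given, and neither is called the main analysis. No covariate is mentioned for either.

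Section 2.5 says that children are "randomly assigned to the treatment group or control group at a ratio of 1:1" and that "Randomization was performed without any stratification". Section 2.4 admits children "aged> 6 months and <16 years old". The limitations at the end of the Discussion accept that "factors such as the age of the patients included in the study may have an impact on the results".

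Section 2.3 states that "The calculation of the sample size is based on the results of the 6 MWTD" (6-minute walking distance). Section 2.7 restricts that test to children able to cooperate with walking. It states measurement before and after treatment for SpO2 and brain natriuretic peptide, but not for walking distance.

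**The concern.** The plan identifies age as influential and then handles it in neither the allocation nor the stated between-group test. Age is known at entry for every child, and the baseline value of an outcome is usually one of its better predictors. Variation in the month-6 value that these two variables explain stays in the error term of a one-way ANOVA. The cost is a wider confidence interval and lower power, in a trial that expects to keep only about 33 children per arm.

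The plan also leaves two analyses of the same outcomes side by side without saying which one answers the trial's question. The Bonferroni post-hoc step on group has a single comparison to correct, because there are only two arms, so it changes nothing.

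**Working it through.** **Inputs from section 2.3.** Means 495.47 and 456.33, so the difference is δ = 39.14 m. SDs 54.72 and 54.68, so the pooled SD is σ = √[(54.72² + 54.68²)/2] ≈ 54.70 m. The SDs are taken to describe the end-of-treatment value. Level 5% (sidedness not stated), power 90%, 34 per group, 20% withdrawal, 42 enrolled per group.

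**The plan's own figure.** n = 2(u_α + u_β)²σ²/δ².
- One-sided 5%: 2 × (1.645 + 1.282)² × 54.70²/39.14² = 33.45, so 34. This reproduces the stated figure.
- Two-sided 5%: 2 × (1.960 + 1.282)² × 54.70²/39.14² = 41.04, so 42. This does not.

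The F test of a two-group one-way ANOVA is two-sided, so the two-sided level is used below.

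**Evaluable children.** 42 × 0.8 = 33.6, taken as n = 33 per arm. This assumes that every retained child can do the walk test.

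**Unadjusted test.** SE = 54.70 × √(2/33) = 13.47 m. Noncentrality = 39.14/13.47 = 2.91 on 64 df. Two-sided power (noncentral t) is **81.7%**.

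**ANCOVA with two covariates.** SE = σ√(1 − R²) × √(2/33) × √(1 + 2/61), on 62 df. R is the multiple correlation of the outcome with baseline value and age within arms. The last factor (variance × 1.033) and the two lost degrees of freedom are the price of estimating two slopes. The documents do not give R, so a range is shown.

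| R (assumed) | 1 − R² | SE (m) | Two-sided power |
|---|---|---|---|
| 0 | 1.00 | 13.69 | 80.4% |
| 0.3 | 0.91 | 13.05 | 83.9% |
| 0.5 | 0.75 | 11.85 | 90.2% |
| 0.7 | 0.51 | 9.77 | 97.6% |

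**If the multiway ANOVA is group by time.** With two time points, the interaction compares mean change between arms. Assuming equal variances at both times and baseline–final correlation ρ, the variance factor relative to raw final values is 2(1 − ρ). For ANCOVA on baseline it is 1 − ρ², before the small penalty above.
- ρ = 0.3: 1.40 against 0.91. The change score is worse than raw values.
- ρ = 0.5: 1.00 against 0.75. Change-score power is 81.7%, the same as for raw values.
- ρ = 0.7: 0.60 against 0.51. Change-score power is 95.9%.

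**The case against.** The strongest reply is that an unadjusted comparison after randomisation is valid, that covariate lists often sit in an analysis plan, and that a journal article is condensed. The first part stands in full: this is a matter of precision, not of error. The rest has less force, because the article does not leave the method open. It names a covariate-free test.

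A second reply is that the multiway ANOVA may already use the baseline value. That may be so, and at a high correlation little is then left to gain from baseline alone (95.9% against 97.6% at 0.7). At 0.5 the change score gains nothing, below that it loses, and nothing in the text says that either ANOVA includes age.

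Three stronger readings are tempting, and the documents do not support them.
- *Chance age imbalance biases the result.* If walking distance correlated 0.6 with age (assumed), a one-SE imbalance at 34 per arm would move the difference by 0.6 × 54.7 × √(2/34) = 8.0 m. That movement is already part of the unadjusted SE of 54.7 × √(2/34) = 13.3 m. It is not an extra exposure, and on average it is zero.
- *Missing covariates explain the shortfall from 90% power.* They do not. The shortfall arises because 34 per group is a one-sided figure.
- *Adjustment is free and the data are already in hand.* It costs two degrees of freedom, and a baseline walk test is only implied. Restricting the test to children who can walk also narrows the age spread for that outcome, so the gain from age may be smaller than the full eligibility range suggests.

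**Conclusion.** The point holds as a recommendation to improve a stated method. The unadjusted one-way ANOVA is legitimate but probably less efficient than an ANCOVA on baseline value and age, in a trial that concedes age may matter and does not stratify by it. At 33 evaluable per arm and a two-sided 5% level, the gain over 81.7% power is about 2 points at R = 0.3, 8 to 9 points at 0.5 and 16 points at 0.7. The loss is about 1 point if the covariates predict nothing.

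These figures rest on the plan's own difference and SD, on 20% withdrawal, on every retained child completing the walk test, and on an assumed correlation. If the multiway ANOVA is a group-by-time analysis, the advantage over it is smaller at high correlations. It should not be read as a claim that the planned test is biased or that its P value would be wrong.

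**What to change.** In section 2.9, name one main between-group analysis for continuous outcomes: ANCOVA of the month-6 value on treatment, with the baseline value and age (continuous) as covariates, reporting the adjusted difference and its 95% CI. Use the same model for the other continuous indices. State the factors of the multiway ANOVA and its role beside the ANCOVA, or remove it. Delete the Bonferroni post-hoc on the two-level group factor. In section 2.7, confirm that walking distance is measured at baseline in children able to walk.

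The cost is a change of wording, preferably made before unblinding, plus two degrees of freedom in the analysis. If no baseline walk is currently planned, adding it is a further measurement.

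The mismatch between a one-sided sample size and a two-sided test should be corrected in section 2.3 in its own right. An assumed gain from adjustment should not be used to cover it.

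### The group-over-time test is named as a multiway ANOVA with no term for the child, although the same children are measured before treatment and at month 6

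*Protocol article*

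**What the plan says.** Section 2.9 (Statistical analysis) gives continuous outcomes two analyses. For the first, "differences between groups were analyzed using a series of one-way analysis of variance (ANOVA) with Bonferroni posthoc test". For the second, "differences between groups over time were analyzed using multiway ANOVA with Bonferroni posthoc test". A single threshold covers both: "A *P* value of <.05 was considered statistically significant". The section mentions no repeated-measures factor, subject term, mixed model or baseline covariate, and does not say which term of the multiway model is the treatment effect.

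The data are paired within child. Section 2.7 (Observation index) says to "measure SpO2 before and after treatment in the 2 groups", and for brain natriuretic peptide "The patient got 5 ml of fasting venous blood in the morning before and after treatment". Section 2.6 (Intervention) sets six months of treatment and says to "review the observation indicators at the sixth month". Months 1 and 3 are for symptoms and adverse reactions, so the group-by-time comparison has in effect two time points.

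**The concern.** A factorial group-by-time ANOVA has one residual variance and takes every observation as independent. Two values from one child are normally positively correlated. The model therefore misjudges the precision of any term that combines a child's two values.

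The group main effect averages each child's two values. Its standard error comes out too small, so it rejects too often. It also averages the month-6 effect with baseline, where randomisation leaves no systematic difference, so the effect it estimates is halved.

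The time and group-by-time terms rest on differences within a child. Their standard errors come out too large, so they reject too rarely. Group by time is the term that most directly expresses a difference between groups over time. The practical loss is therefore mainly of power there, with a risk of false positives if the group main effect were read as evidence of efficacy.

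**Working it through.** **Inputs.** From section 2.3: experimental mean 495.47 and SD 54.72; control mean 456.33 and SD 54.68; 34 per group. The difference is δ = 495.47 − 456.33 = 39.14 m and the common SD is σ = √[(54.72² + 54.68²)/2] = 54.70 m. Assumed, because the article does not give them: a within-child correlation ρ of 0.3, 0.5 or 0.7; the same SD at baseline and month 6; a treatment effect at month 6 only; two time points. Tests are two-sided at 5%.

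**The plan's own figure.** "At the 5% significance level, a total of 34 patients are required for each group to achieve 90% power". The printed formula gives 2 × (1.645 + 1.282)² × 54.70² / 39.14² = 33.45, so 34, with a one-sided 5% critical value. With the two-sided value 1.960 it gives 41.04, so 42. The article does not state sidedness. That is a separate matter; 34 per arm is used here because it is the planned evaluable number.

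**Standard errors with n = 34 per arm.** The single-residual model estimates σ² correctly but applies it as if ρ were 0.

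- Group main effect: model SE = σ/√n = 9.38; true SE = σ√[(1+ρ)/n]. The model SE is too small by a factor √(1+ρ).
- Group by time (difference in mean change): model SE = σ√(4/n) = 18.76; true SE = σ√[4(1−ρ)/n]. The model SE is too large by a factor 1/√(1−ρ).
- ANCOVA at month 6: SE = σ√[2(1−ρ²)/n].
- One-way ANOVA at month 6: SE = σ√(2/n) = 13.27, whatever ρ is.

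**Type I error at nominal 5%.** Group: 2[1 − Φ(1.96/√(1+ρ))]. Group by time: 2[1 − Φ(1.96/√(1−ρ))].

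**Power for 39.14 m.** Single-residual group by time: Φ[(39.14 − 1.96 × 18.76)/true SE]. The others: Φ(39.14/SE − 1.96). For example, at ρ = 0.5 the true interaction SE is 13.27. The single-residual test then has Φ(2.37/13.27) = Φ(0.18) = 57%, and the correct test has Φ(2.95 − 1.96) = 84%.

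| Normal approximation | ρ = 0.3 | ρ = 0.5 | ρ = 0.7 |
|---|---|---|---|
| True SE, group main effect | 10.70 | 11.49 | 12.23 |
| True SE, group by time | 15.70 | 13.27 | 10.28 |
| SE, ANCOVA | 12.66 | 11.49 | 9.47 |
| Type I error, group | 8.6% | 11.0% | 13.3% |
| Type I error, group by time | 1.9% | 0.6% | 0.03% |
| Power, group by time, single residual | 56% | 57% | 59% |
| Power, group by time, within-child error | 70% | 84% | 97% |
| Power, ANCOVA | 87% | 93% | 99% |
| Power, one-way ANOVA at month 6 | 84% | 84% | 84% |

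Simulation with the exact t and F tests agrees to within about two percentage points. Type I error is about 9, 11 and 13% for group and 2, 0.6 and under 0.1% for group by time. Power is about 55, 56 and 58% for the single-residual interaction, 69, 83 and 97% with a within-child error term, and 86, 91 and 98% for ANCOVA. At ρ = 0 all the ordinary tests return to about 5%.

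**Post-hoc tests.** The model's residual estimates the variance within a group-by-time cell, which is the right variance for comparing two independent arms at one time. Simulated before Bonferroni adjustment, the month-6 between-arm contrast has about 5% type I error and 83 to 84% power at each ρ. The before/after contrast within one arm does use the wrong error: it rejects a true null in about 2, 0.6 and under 0.1% of trials.

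**The case against.** Four points can be made for the plan.

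*Multiway ANOVA may mean a repeated-measures ANOVA.* The article does not call the model ordinary, and a multiway ANOVA with the child as a random or blocking factor would be valid. This is possible, but no such term is stated, and an analyst who followed the wording literally would fit the single-residual model. The wording needs correcting on either reading.

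*A valid test is already there.* This stands. With two arms, the one-way ANOVA at month 6 is a two-sample t-test. It matches the sample-size formula and is untouched by within-child correlation. A reader might infer that the trial has no sound test of its question, or that every P value is wrong; the article does not support that. However, section 2.9 puts the over-time analysis beside the one-way test at the same threshold and makes neither primary.

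*The inflated main effect may never be used.* This also stands. A reader might infer that efficacy will be claimed from a test with 9 to 13% type I error. The article does not say so, and its phrase about differences over time points more naturally to the interaction, which is conservative.

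*The size is assumed.* No correlation is given, and section 2.7 attaches before-and-after wording to SpO2 and natriuretic peptide, not explicitly to walking distance. The percentages are therefore illustrative. The direction of both errors needs only a positive correlation.

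A reader might also infer that all the Bonferroni post-hoc tests fail. They do not: only the within-arm before/after contrasts do.

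**Conclusion.** The point holds for the multiway ANOVA as named. Without a child term, its group main effect is too liberal and its time and group-by-time tests too conservative. Under the assumed correlations, group-by-time power is about 55 to 58%, where a correct error term would give 69 to 97% and ANCOVA 86 to 98%. These figures rest on equal variances, two time points, 34 evaluable children per arm and a month-6-only effect of 39.14 m. A correlation near zero would remove the problem; a higher one would worsen it.

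It should be fixed before analysis, but it is not fatal, because the month-6 one-way ANOVA is valid with about 83% power.

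**What to change.** In section 2.9, replace the multiway ANOVA with ANCOVA of the month-6 value on treatment and the baseline value. Report the adjusted difference with its 95% confidence interval as the treatment effect.

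If a group-by-time analysis is kept, declare the child as the repeated-measures subject and name group by time, or the month-6 contrast, as the treatment effect. Naming the subject is enough to restore a 5% type I error. ANCOVA is preferred because it is more powerful than the interaction at every correlation tried, and more powerful than the unadjusted month-6 comparison. Before/after contrasts within an arm should use the within-child error or be dropped.

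The cost is about two sentences. The methods are available in the software already named, and no new data are needed provided the baseline values are recorded.
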